## Abstract

Life expectancy has increased unprecedentedly in recent decades, benefiting the longevity of the world’s population. The most frequent pathological conditions presented in this age group include excessive body fat, frailty, and hypercholesterolemia. These pathological characteristics condition general health and autonomy in adults to carry out their usual activities. In this sense, the search for a healthy lifestyle is necessary, consisting in a healthy diet that includes supplementation with nutraceuticals and the daily practice of physical activity. This study protocol aims to evaluate the independent and synergistic effect of 12 weeks of *Spirulina maxima* intake (5 g/day), with or without an exercise program on metabolic and fitness parameters of 52 sedentary older adults with excessive body mass in a double-blind, randomized, crossover, controlled trial design. The main findings from this trial will provide novel evidence for future interventions designed for the elderly population and the result will be disseminated through peer-reviewed journals and international meetings. ClinicalTrials.gov identification number: NCT04658875 (Effect of *Spirulina maxima* and Exercise on General Fitness and Blood Lipids in Older Adults).

## 1. Introduction

Life expectancy has increased unprecedentedly in recent decades, benefiting the longevity of the World’s population, with projections of a growth in the population older than 60 years from 900 million in 2015 to two billion in 2050 [1], this means that the older population will move from 12% to 22% of the global population in the next years. For the elderly population, the most frequent health conditions include excessive body fat, frailty, and hypercholesterolemia [2]. Some of these conditions can co-exist in aging individuals, presenting new challenges, for example, the combination of excessive body fat and reduced muscle mass or strength, recently defined as sarcopenic obesity [3]. Muscle protein breakdown is one of the main contributors to chronic low-grade inflammation and sarcopenia. Recent studies suggest that the progression of muscle fiber anabolism and muscle wasting is highly related to the reduction of the endogen antioxidant system and oxidative stress, inducing the activation of muscular autophagy mechanisms [4].

These phenomena are a major concern, given that it compromises general health, physical ability (i.e., autonomy to carry out their daily life activities such as walking, eating, preparing or buying food, and bathing, among others) and mortality rate [5]. That means that the elderly population are at increased risk for developing some disease or dependence during their last years of life.

Overweight, obesity and dyslipidemias contribute considerably to the burden of cardiovascular diseases and exacerbate the age-related decline in physical function, which causes frailty and impairs quality of life [6]. Many of the available conventional treatments aimed at reducing these risk factors often have collateral side effects, leading older people to often use complementary medicine instead. Thus, the pharmacological industry has focused on developing new treatment options, in this sense, the search for a healthy lifestyle is needed, which covers a healthy diet that includes supplementation with nutraceuticals and daily physical activity [7].

Regarding supplementation with nutraceuticals, the cyanobacterium *Spirulina maxima* (*S. maxima*) presents antioxidant compounds, which has been associated with beneficial cardiovascular effects [8] also it has important benefits to reduce non-communicable diseases, alone or in combination with exercise, mainly in animal models [9]. Recently, studies on *S. maxima* effects focus on verifying its components’ biological activity, including general fitness improvements and hypolipidemic effects [10]. It has been shown that liver lipid accumulation (as well as the visceral in general), can be reduced by modulating the infiltration of macrophages by Spirulina compounds [11]. However, given that these investigations were mainly carried out in animals, appropriate clinical trials are necessary [12] to add knowledge in the beneficial effect of *S. maxima* in humans.

Furthermore, performing exercise has been widely reported to reduce the risk of hypertension, diabetes, and hypercholesterolemia [13]. In this context, moderate intensity-physical exercise has exerted the best protective effect, mainly attributed to metabolic adaptations [14]. The effects of performing exercise programs in older adults have shown a reduction on adiposity and serum lipid levels [15], and also a reduction in sarcopenia markers, such as improvement in muscle mass, muscle strength, and physical performance [16]. Exercise has also been included as part of multicomponent interventions targeting physical function in older adults living in poverty in rural communities with significant results [17]. Thus, appropriate exercise prescription methods need to be implemented, in this sense, the rating of perceived exertion scale [18] and the Talk Test [19] are no-invasive, easy access, and validated subjective methods to estimate exercise training intensity by self-evaluation of the intensity of a physical activity perceived and the difficulty to speak comfortable during a 30 speech, respectively.

Therefore, we hypothesize that the administration of *S. maxima* alone or together with an exercise plan will decrease the body fat percentage and blood lipids while increasing physical function in sedentary elderly patients with excessive body mass in a randomized, double-blind, counterbalanced, crossover, controlled trial. The main objective of our research is to evaluate the independent and synergistic effect of 12 weeks of *S. maxima* intake (compared to placebo), with or without an exercise program on the body composition (body fat percentage, muscle mass percentage, and body mass index (BMI)) in sedentary older adults with excessive body mass. The secondary objective is to test the effects of both interventions in the blood lipid profile, energy intake, physical function, sleep wake patterns, mental health, and inflammation, as well as to analyze the influence of the genetic background in all outcomes in older adults with excessive body mass.

## 2. Materials and Methods

This study is designed according to the standard protocol requirements for clinical trials (SPIRIT) (Supplementary File 1) and will be conducted and reported in keeping with the Consolidation Standards of Reporting Trials (CONSORT).

### 2.1. Eligibility Criteria

Fifty-two sedentary (daily energy expenditure <4 METs, as measured by a continuous physical activity questionnaire (IPAQ)) [20] older adults (≥60 years) with a BMI over 25 kg/m^2^ volunteered to participate will be recruited by personalized interviews including a Physical Activity Readiness-Questionnaire for Everyone (PAR-Q+) [21] conducted to ensure eligibility. The participants inclusion and exclusion/elimination criteria are depicted in Table 1.

### 2.2. Interventions

The clinical trial consists of two interventions: (1) supplementation with *S. maxima* (5 g/day) or placebo (5 g/day of a low-calorie saccharine), and (2) an exercise program, during a period of 24 weeks in a randomized, double-blind, counterbalanced, crossover, controlled trial with a 2 × 2 factorial design. Presentation of both supplements will be powder encapsulated in dark capsules of 0.5 g to present the same organoleptic attributes and mask their individual characteristics.

Inclusion in the exercise program intervention will be decided by each participant, who will be randomly assigned to one of the two possible nutritional interventions (*S. maxima* or placebo) categorized into four treatments: an exercise program plus *S. maxima* intake; exercise with placebo administration; *S. maxima* intake without exercise, or placebo supplementation without exercise program (Control). To assess compliance to the supplement intake, a crossover will be conducted for the supplementation interventions.

The first period of treatment will be carried out for 12 weeks, followed by a four-week wash-out period to avoid any possible delayed effect of *S. maxima* in the organism. Finally, a further 12 weeks of treatment for the second intervention groups (Figure 1).

Due to absence of data related to wash-out and treatment periods length, we considered 4 and 12 weeks, respectively, as stated by a systematic review of clinical trials that used spirulina as treatment [22].

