### 2.4. Allocation and Sample Size

The initial allocation will be performed in such a way that each group had almost the same proportion of *S. maxima*:placebo (1:1) supplemented individuals through the RandomizeR package of the R version 4.0.2 statistical software [34]. Participants’ group allocations will be performed by an independent researcher, who does not have any other involvement during the study, break of double-blind (participants and principal investigators) can occur only in exceptional circumstances and must be immediately reported. Sample size was calculated considering a level of significance of 0.05 with a study power of 0.85, selecting a sample of ≥52 participants. The statistical software G*Power (v3.1.9.7, Universität Kiel, Düsseldorf, Germany) [35] was used to determine the sample size.

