### 2.6. Statistical Methods

Normality and homoscedasticity of variables will be screened by the Shapiro–Wilk and the Levene tests, for each group. The analysis of statistical differences among treatments and time, univariate repeated measures ANOVA with two within-participants (initial and final values), and four inter-participants (treatments) factors will be used. Moreover, basal and post-treatment values will be contrasted by paired *t*-tests. Delta values will be analyzed by one-way ANOVA and Tukey Post-hoc tests (normal distribution and equal variances) and Kruskal-Wallis H and Dunn’s Post-hoc test (non-parametric distribution and unequal variances), with Bonferroni setting for multiple comparisons. Spearman correlations will be run to evaluate the associations among variables. Eventual gen-diet and gen-exercise interactions concerning anthropometric and metabolic outcomes will be assessed by univariate regression analyses. Statistically significance will be set at a *p*-value of 0.05. All statistical analyses will be completed using IBM SPSS package version 23 (SPSS Inc, IBM Company, Chicago, IL, USA) and STATA software (StataCorp, College Station, TX, USA).

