## 3. Discussion

The SIE study will be the first examining the synergistic effect of *S. maxima* intake and exercise on adiposity, physical function, serum lipids, mental health, sleep-wake patterns and inflammation, as well as to analyze the influence of the genetic background in these outcomes in older adults, using a double-blind, randomized, crossover trial. Because of the double-blind design, the described methodology and a higher number of participants than other studies [22], it is expected to achieve better support for the hypothesis that *S. maxima* will have hypolipidemic effects and improve on adiposity and physical function together with an exercise program in sedentary older adults with excessive body mass. It is noteworthy that not every overweight or obese patient has problems with lipid metabolism. The association between increase of body fat and lipid alterations is well known [37]. For that reason, the primary focus of this protocol is prevention, which is why we do not consider dyslipidemia as an inclusion criterion even though it could be present in this condition. Finally, it is known that the practice of exercise and a balanced diet stimulate the reduction of body mass in obese people and generally decreases cardiometabolic risk factors, so it probably generates an increase in physical capacity [38]. However, apparently no studies on the decrease in metabolic oxidation by Spirulina’s administration in elder individuals with excessive body mass have been performed. Hence, well-designed studies are needed to examine the therapeutic value of *S. maxima* supplementation in clinical practice and its synergetic effect with or without exercise to reduce dyslipidemias and body fat in overweight and obese people, a fact almost unknown lately [39]. This establishes that the importance of this study is to contribute in the advancement in the frontiers of knowledge.

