### Strengths and Limitations

Even though the present study will show evidence of *S. maxima* supplementation’s clinical importance, the variety of bioactive compounds contained in *S. maxima* limits the possibility of establishing clear and specific action mechanisms. Concerning to the inclusion criteria, only sedentary older adults with BMI over 25 kg/m^2^ will be selected, so the overall results may not translate to other populations of older adults. Another limitation is that the randomization will not be applied to define the inclusion or not in the exercise program intervention, it will be decided by each participant since the personal decision to belong to the exercise group will reduce severely the possibility of study desertion [40,41]. In addition, the beneficial effects associated with healthy lifestyles (physical exercise and nutraceuticals) underlie major causes such as sociodemographic characteristics of the participants, timing of the intervention, dose of supplementation, environmental factors, and genetic background [42]. Previous studies display a considerable amount of risk of bias, such as selection bias (e.g., recruitment of an over-proportionated number of women) and performance bias (e.g., unclear methods of blinding and concealment). Therefore, a proportional number of women and men will be included in this study. Regarding the sample size, the duration of the intervention and the quantity of *S. maxima* to administrate, double-blind studies have reported on the benefits of four weeks of supplementation with nine participants [43], and other studies have reported on the beneficial effects of supplementation with one g/day of *S. maxima* for 12 weeks [44]. All this establishes the importance of this study.

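### Section 2.2 calls both interventions a randomised, double-blind factorial, but exercise is self-selected and open, and section 2.6 does not separate the four non-randomised exercise contrasts from the randomised ones.

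*Protocol article*

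**What the plan says.** Section 2.2 lists two interventions, supplement and exercise programme, and places both in a "randomized, double-blind, counterbalanced, crossover, controlled trial with a 2 × 2 factorial design". Its next paragraph says "Inclusion in the exercise program intervention will be decided by each participant", and the same sentence describes the participant as one "who will be randomly assigned to one of the two possible nutritional interventions". Random assignment therefore covers S. maxima or placebo only. Masking (identical dark capsules) and the crossover also apply only to the supplement.

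Section 2.4 gives a 1:1 ratio for the supplement, so that "each group had almost the same proportion of" S. maxima and placebo. It gives no ratio for exercise to no exercise.

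Section 2.6 states the main analysis: "univariate repeated measures ANOVA with two within-participants (initial and final values), and four inter-participants (treatments) factors will be used". Change scores then go to one-way ANOVA with Tukey tests, or to Kruskal-Wallis with Dunn tests. Nothing there distinguishes contrasts that rest on randomisation from those that do not.

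The main objective, at the end of the Introduction, is the independent and synergistic effect of the supplement, with or without exercise, on body composition, which is the primary outcome in section 2.3. Section 3 opens by attributing the synergy result to a double-blind, randomised crossover trial. Strengths and Limitations acknowledges that "randomization will not be applied to define the inclusion or not in the exercise program intervention" and gives retention as the reason.

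**The concern.** People who opt for five sessions a week are likely to differ from those who decline in ways that affect how their body composition changes over 12 weeks, such as current activity, diet and motivation. A comparison across exercise status then mixes the effect of exercise with the effect of who chose it. Knowing one's own exercise status can also alter behaviour and performance, and capsule masking does nothing about that.

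The stake is the primary objective. S. maxima plus exercise versus control is the comparison most readers will look at, and it crosses exercise status. If it is reported beside the randomised contrasts under a single design label, it acquires a causal standing that the allocation cannot give it. The same holds for the word synergy when it is read as something that exercise causes.

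**Working it through.** **Which contrasts are affected.** Four treatments give 4 x 3 / 2 = 6 pairwise contrasts. Two stay within an exercise status (S. maxima versus placebo among exercisers, and the same among non-exercisers) and are randomised. The other 2 x 2 = 4 cross exercise status and are not.

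**What bias is left in a change score.** Let b be the difference in mean change, in SD of the change score, that choosers and non-choosers would show with no exercise effect at all.

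- Exercise contrast: expected difference = exercise effect + b. A stable difference in level cancels in the change score, so b reflects only different change over time.
- S. maxima versus placebo within a stratum: b is on both sides and cancels.
- Supplement x exercise: (SE - PE) - (S - P), where SE and PE are the mean changes on S. maxima and placebo in exercisers, and S and P those in non-exercisers. Again b cancels. If choosers respond to the supplement differently by h, the contrast equals h even when exercise itself does nothing.

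**Inputs.** N = 52 and alpha 0.05 come from section 2.4. The documents give no size for b and no exercise split. Both are assumed here: b = 0.2, 0.3 or 0.5 SD, and 26 exercisers with 26 non-exercisers, that is 13 per treatment. One period is considered; pooling the two periods would change the rates.

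**Planned test: Tukey on change scores.** With 4 groups and 48 error df the 5% studentised-range point is 3.764, so two cells must differ by 3.764 x s / sqrt(13) = 1.04 s. Simulated rejection rates with no true effect:

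| b (SD) | any of the 4 exercise contrasts | S. maxima + exercise vs control |
|---|---|---|
| 0 | about 4% | about 1% |
| 0.2 | about 7% | about 2% |
| 0.3 | about 11% | about 4% |
| 0.5 | about 25% | about 9% |

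**Pooled exercise versus no exercise, for comparison.** This is a two-sample t-test with 50 df and critical value 2.009. Noncentrality = b / sqrt(1/26 + 1/26) = b x sqrt(13), which is 0.72, 1.08 and 1.80. Rejection rates are 10.9%, 18.6% and 42.4%. With an uneven 14/38 split, sqrt(13) is replaced by sqrt(14 x 38 / 52), and the rates are 9.6%, 15.6% and 34.8%. Section 2.6 does not specify this pooled test; it shows what an exercise main effect would do.

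**Specificity.** In 4,000 simulated 2 x 2 analyses with b = 0.5 SD and no true effects, exercise was significant in 43.5% of runs, the supplement in 4.9% and the interaction in 5.8%. With h = 0.5 SD added, the interaction estimate averaged 0.51 SD, although exercise had no effect.

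The sample size of 52 does not enter as a claim to be checked: section 2.4 gives no effect size or test from which it could be reproduced.

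**The case against.** The strongest reply is that nothing is hidden. The Methods themselves say that exercise is chosen and that random assignment is to the nutritional interventions, section 2.4 gives a ratio for the supplement only, the limitation is stated, and section 2 commits to CONSORT reporting. This stands. A reader might infer that the sponsor will present exercise effects as randomised results; the documents do not show that, and it would be a prediction about a later paper. What can be said is that the acknowledgement leaves the label in 2.2, the framing in 3 and the comparison in 2.6 as they are.

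Several narrower replies also stand:

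- Section 2.6 does not itself use the words randomised, double-blind or factorial, and section 3 does not say factorial. The full label is in 2.2 only. The fault in 2.6 is the undifferentiated comparison.
- The sentence in section 3 beginning "Because of the double-blind design, the described methodology and a higher number of participants than other studies" mainly concerns S. maxima, which is blinded. The opening sentence of that section, on synergy, is the firmer support.
- Covariate lists are commonly left to an analysis plan, which is not shown. Their absence is not the point here.
- Change scores remove stable differences between choosers and non-choosers.
- Motivation is not among the recorded variables, so adjustment cannot remove all confounding.
- The pooled 26 versus 26 figures overstate what the planned Tukey tests would do, and any further Bonferroni correction would lower the rates again.

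**Conclusion.** The point holds in a limited form. The randomised, double-blind description is accurate for the supplement and inaccurate for exercise, and section 2.6 handles randomised and non-randomised contrasts alike. The four contrasts that cross exercise status are open to confounding through differential change over time.

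Two stronger readings are not supported. One is that the whole trial is compromised: S. maxima versus placebo, overall or by stratum, keeps its randomisation and masking. The other is that the interaction is confounded in the same way: it compares two randomised effects and is a valid comparison, but it shows effect modification by chosen exercise status, not synergy caused by exercise.

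On size, assumed selection differences of 0.2 to 0.5 SD in change raise the chance of at least one falsely significant exercise contrast from about 4% to between 7% and 25% under Tukey with 13 per cell, and the pooled exercise test from 5% to between 11% and 42%. These are illustrations, because neither the bias nor the exercise split is given. The inferential limit on the exercise contrasts does not depend on them.

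**What to change.** - **Sections 2.2 and 3:** describe the trial as a randomised, double-blind crossover of S. maxima versus placebo within two self-selected exercise strata.
- **Section 2.6, confirmatory claims:** limit these to the within-person S. maxima versus placebo contrast, overall and by stratum.
- **Section 2.6, supplement x exercise:** report it as effect modification by chosen exercise status.
- **Section 2.6, exercise contrasts:** label them non-randomised and unblinded. Adjust for day-0 outcome, age, sex, baseline IPAQ activity and baseline energy intake. Use no causal wording even after adjustment, because unmeasured factors such as motivation remain.
- **Self-selection:** keep it, given the stated retention reason.

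The cost is rewording in three sections and a model that uses data already being collected, with no new visit or measurement. The downside is that the exercise claim becomes weaker.

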#### 2.2.1. Exercise Program

Participants in the exercise program groups will exercise five days a week. The physical activity program will be conducted in accordance with the American College of Sports Medicine recommendations [23] and will consist of Monday to Friday chair exercises performed during 24 weeks.

The approximate exercise duration will be of 40–50 min. Each exercise session has an initial or warm-up phase of 5–10 min (joint movement exercises to increase body temperature starting with movements of head, upper extremities trunk, hip, and, lower extremities); a main physical conditioning phase of 25–30 min that will consist of developing a personalized circuit of strength exercises of the main muscle groups (arms, shoulder, chest, back, and legs) at moderate intensity (between 3.0 and 6.0 metabolic equivalents of task (METs)) using rating of perceived exertion scale and the Talk Test; finally, a cool-down or relaxation phase of 5–10 min. To define the individual exercise intensities in the main physical conditioning phase, participants will have a training of 3 to 5 days before the beginning of the clinical trial to learn how to use the rating of perceived exertion scale and the Talk Test as markers of exercise training intensity.

Trained personnel will assist older adults to perform the exercise program, including articular flexibility, postural exercises, and proprioception exercises. These activities will be selected according to the individual deterioration and joint stiffness that the participants could present. Researchers are trained in cardiopulmonary resuscitation and the laboratory has the necessary tools and communication channels to carry out emergency procedures if a participant presents any side effect of exercise.

